#### 261 *Sample size*

262 We calculated the sample size on the basis of the primary outcome. A previous systematic review  
263 assessing the effects of computer reminders delivered to clinicians at the point-of-care on health care  
264 processes and outcomes found a median improvement of 4.2% in process adherence across all reported  
265 process outcomes [57]. Accordingly, assuming resolution rates of 5% in the intervention group versus  
266 3% in the control group due to a possible group contamination, we calculated that a sample of 4,230  
267 reminders will be necessary to detect the difference between the two groups (power = 0.90;  $\alpha$  = 0.05,

two-sided; 1:1 allocation). Because estimates for intracluster correlation are not available, we increased the required sample size (by 10%) to 4,650 reminders to account for clustering by patient. Moreover, based on a prior study evaluating EBMeDS, which recorded an average of 0.30 reminders per individuals triggered at baseline [58], we determined that a total number of 15,500 patients (7,750 per group) need to be enrolled. This figure corresponds to a conservative estimate of the recruitment period of 24 months for the internal medicine departments of the Vimercate Hospital.

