### *Allocation and blinding*

Anonymous patient identification (ID) numbers in the EHR system will be the unit of randomization. An individual external to the study group will generate the anonymous IDs using a formula based on patients' unique fiscal code numbers.

We will randomly assign patients to either the control or experimental group with a 1:1 allocation. We will follow a computer generated randomization schedule stratified by gender and age (0–30, 31–60, 61–80, >80 years) using permuted blocks of random sizes [59]. Patients will be randomized immediately after the first launch of their EHR (entry of demographic data by physicians at hospital admission), and the allocation will be maintained through successive admissions.

Patients and study investigators (i.e., researchers, statisticians, information technology specialists, and hospital representatives) will be blinded to the allocation of participants. We will maintain the blinding up to the dataset disclosure. On the other hand, blinding of physicians is not feasible due to the nature of the intervention: the physician will know that a patient has been allocated to the intervention group if an automatic, patient-specific reminder is displayed on the screen.

292    ***Data collection***

293    The data collection for this study will follow the standard data collection procedures of the AODV. We  
294    will collect demographic (i.e., gender, age) and administrative (i.e., anonymous patient ID, admission  
295    and discharge dates, diagnoses) data from the EHR archive on a daily basis. Information on reminders,  
296    including all scripts that have been activated in a patient’s record, will also be collected daily, but  
297    during the night, so as not to disturb or slow down the use of the patient EHR.

298

299    ***Statistical methods***

300    For the primary outcome (i.e., resolution rates), the reminder will serve as the unit of analysis, and the  
301    patient the clustering factor. The patient will be the unit of analysis for the secondary outcomes (i.e.,  
302    length of stay and in-hospital mortality). All analyses will follow the intention-to-treat principle:  
303    patients will be analyzed in the group to which they have been randomized. Descriptive statistics will  
304    be presented as means  $\pm$  standard deviations (SD), medians and interquartile ranges (IQR), or  

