305    percentages when appropriate. We will compare continuous variables using the Student’s *t*-test when  
306    normally distributed, and the non-parametric two-sample Wilcoxon rank-sum (Mann-Whitney) test  
307    when they are not normally distributed. We will compare categorical variables using the chi-squared  
308    test or the Fisher’s exact test, as appropriate. To model the resolution rates of the reminders, we will  
309    run a random effects logistic regression analysis, accounting for clustering by patient [60].

310    For hypothesis testing, we will consider a probability level of less than 0.05 as statistically significant.  
311    All statistical tests will be two-sided. We will use the Stata software to perform all statistical analyses  
312    (Stata Corp., College Station, TX, USA).

313

314    ***Data monitoring***

315    Data monitoring will inform the CODES trial conduct, identifying the potential need for adjustments:

316 (i) **Sample size recalculation:** Because the sample size calculation utilizes several assumptions, we will  
317 analyze the first batch of data collected and adjust the estimated sample size, if necessary, at the end of  
318 the sequential roll-out of the intervention. The 24-month recruitment period may also be adjusted,  
319 accordingly.

320 (ii) **Interim analysis:** We will perform an interim-analysis on the primary endpoint after 50% of the  
321 patients have been randomized, after 50% of the expected events have occurred, or after 12 months of  
322 the study's initiation (the assumed half-life of the trial), whichever occurs first. An independent  
323 statistician that is blind to the patient allocation will perform the analysis. This analysis will inform  
324 whether the intervention has been proven for efficacy (beyond reasonable doubt). We will subsequently  
325 decide whether (or not) it is necessary to modify the study or prematurely terminate it, if necessary.

326 (iii) **End of trial:** The end of trial will occur thirty days after the randomization of the last EHR. We  
327 will submit an End of Trial notification and final report to the competent Ethical Committee, the  
328 AODV, and to the Sponsor.

329

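### Randomisation is stratified by gender and age band, but the tests named for the patient-level secondary outcomes are unadjusted and the primary model names no stratification factor (minor; a free improvement)

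*Protocol*

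**What the plan says.** Under Allocation and blinding, the protocol uses a "computer generated randomization schedule stratified by gender and age" with age cut at 30, 60 and 80 years and permuted blocks of random size. Two genders by four age bands gives eight strata. Data collection confirms that gender and age are both recorded.

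Under Statistical methods, the reminder is the unit of analysis for the primary outcome, and the patient is the unit for length of stay and in-hospital mortality. Continuous variables are compared by t-test or Wilcoxon rank-sum test, and categorical variables by chi-squared or Fisher's exact test. For resolution rates the investigators will "run a random effects logistic regression analysis, accounting for clustering by patient". On testing, "we will consider a probability level of less than 0.05 as statistically significant" and "All statistical tests will be two-sided". Gender and age appear in none of these analyses, and no effect measure is named for the primary outcome.

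Under Sample size, the trial is planned "assuming resolution rates of 5% in the intervention group versus" "3% in the control group due to a possible group contamination".

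**The concern.** Stratified blocks force the arms to agree on gender and age. An unadjusted two-sample test does not know this: its standard error still contains the between-stratum variation that the design has removed. The standard error is therefore too large wherever the strata predict the outcome. Age is likely to predict death and may predict length of stay, and the protocol itself stresses the hospital's elderly and very elderly patients. What is at stake is some precision on the secondary outcomes that the randomisation has already secured.

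A second, smaller matter is the scale of the primary result. The trial is sized on a difference between two proportions, while the natural coefficient of the named model is a patient-specific log odds ratio. The protocol does not say which will be reported.

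**Working it through.** **Inputs from the protocol.** 5% versus 3%, power 0.90, two-sided 0.05, 1:1 allocation, 10% inflation for clustering, 0.30 reminders per patient, eight strata. **Assumed, because the protocol gives none:** mortality by age band, the age mix, the variance explained by the strata (R²), the spread of resolution rates across strata, the intracluster correlation (ICC), and Poisson reminder counts.

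**1. The plan's own figure.** With mean rate 0.04,

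n = [1.96√(2·0.04·0.96) + 1.2816√(0.05·0.95 + 0.03·0.97)]² / 0.02² = 2,015.3, so 2,016 per arm or 4,032 in total.

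With the continuity correction, (n/4)[1 + √(1 + 4/(0.02n))]² = 2,114.2, so 2,115 per arm or 4,230 in total, which is the stated figure. Then 4,230 × 1.10 = 4,653 (stated as 4,650), and 4,650 / 0.30 = 15,500 patients. The sizing is thus on a marginal difference in proportions. Nothing below changes it.

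**2. Secondary outcomes: true size of an unadjusted test.** If the strata are balanced by design and explain a share R² of the variance, the true variance of the difference is about (1 − R²) times the one the test uses. Hence size = 2[1 − Φ(1.96/√(1 − R²))].

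For mortality, assume 1, 3, 8 and 16% across age bands holding 5, 20, 45 and 30% of patients:

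- Mean = 0.0005 + 0.006 + 0.036 + 0.048 = 0.0905.
- Between-band variance = 0.05(0.0805)² + 0.20(0.0605)² + 0.45(0.0105)² + 0.30(0.0695)² = 0.00255.
- Total variance = 0.0905 × 0.9095 = 0.0823.
- R² = 0.00255 / 0.0823 = 3.1%.

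| Assumed R² | 1.96/√(1 − R²) | True size of the 5% test |
|---|---|---|
| 1% | 1.970 | 4.9% |
| 3.1% | 1.991 | 4.65% |
| 5% | 2.011 | 4.4% |
| 10% | 2.066 | 3.9% |
| 20% | 2.191 | 2.8% |

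The power lost is also small. At R² = 3.1%, adjusting raises a comparison with nominal power of 80% from 80.4% to 81.2%, and one with nominal power of 90% from 90.4% to 90.9%.

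**3. Primary outcome.** Take a mean resolution rate of 4% and an assumed ratio of highest to lowest stratum rate between 1.5 and 5. The within-stratum share of the variance is then 0.99961 to 0.99444, and the unadjusted size is 4.996% to 4.94%. At 2,115 reminders per arm and the fivefold spread, power is 0.9142 unadjusted and 0.9151 adjusted, a gain of about 0.1 point.

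Even that is generous, because blocks balance patients and not reminders. With Poisson counts at 0.30, only 1 − e^(−0.3) = 26% of patients have any reminder, so about 74% of the chance imbalance within strata returns. The variance ratio at fivefold spread becomes about 1 − 0.26 × (1 − 0.99444) = 0.9986, and the size about 4.98%.

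**4. Effect scale.** 5% versus 3% is a difference of 2 percentage points and a marginal odds ratio of (0.05/0.95)/(0.03/0.97) = 1.70. The patient-specific odds ratio that gives the same two rates, under a normal random intercept, is:

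| Assumed latent ICC | 0.01 | 0.05 | 0.10 | 0.20 | 0.30 | 0.50 |
|---|---|---|---|---|---|---|
| Conditional odds ratio | 1.70 | 1.71 | 1.72 | 1.74 | 1.77 | 1.90 |

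Of patients with a reminder, 0.3e^(−0.3)/(1 − e^(−0.3)) = 86% have exactly one. About 570 of 15,500 have two or more, and only they inform the random-intercept variance. In simulated trials of the planned size with a true random-intercept SD of 1, the estimate ran from 0 to about 1.7 (5th to 95th percentile). That is a reason to report a rate difference beside the odds ratio. It does not show that the test is biased.

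**The case against.** The strongest reply is that nothing here is invalid. Pre-specified unadjusted tests after stratified randomisation keep type I error at or below 5%. The trial is not sized on mortality or length of stay, and the losses rest on assumed rates. All of this stands, and it limits the point to a minor one.

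A reader might infer that the primary model excludes the strata. The protocol gives only the model class and the clustering unit. It neither lists nor rules out covariates, and a covariate list is commonly left to a statistical analysis plan. For the primary model this is silence. The secondary outcomes differ: the named two-sample tests cannot carry a stratum term, so that is a written choice.

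A reader might also infer that the trial will report a conditional odds ratio in place of the 5% versus 3% difference. The protocol names no effect measure and promises percentages descriptively, and a marginal difference can be derived from the same model. The two odds ratios are close at modest clustering, and under the null both effects are null.

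Nor do the documents show that a random-effects model is the wrong choice. It handles the clustering the protocol identifies, and random effects versus GEE or robust variance is a choice between accepted methods.

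**Conclusion.** The point holds as a minor one. The design stratifies by two recorded factors, the tests named for the patient-level secondary outcomes cannot use them, and the primary model does not mention them. The consequence is conservative: a true size of about 4.65%, 4.4% or 3.9% for secondary outcomes if the strata explain 3.1%, 5% or 10% of the variance, and under 1 point of power in the mortality example. On the primary outcome the effect is close to nil. Type I error is not inflated and the sample size is unaffected. The R² values, age-specific mortality, age mix, spread of resolution rates, ICCs and Poisson counts are all assumptions. The direction of the effect does not depend on them; its size does.

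**What to change.** In Statistical methods (or the statistical analysis plan, with the protocol wording brought into line), state that the analyses follow the randomisation strata, with gender and the four age bands as covariates or strata:

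- In-hospital mortality: logistic regression or a Mantel-Haenszel analysis.
- Length of stay: regression or a stratified rank test.
- VTE-related deaths and events: exact or Mantel-Haenszel methods where events are sparse.
- Resolution rates: the planned random-effects model with the same factors added, for consistency.

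Name the primary effect measure. Since the trial is sized on 5% versus 3%, report a standardised resolution-rate difference with a 95% confidence interval, derived from the planned model, beside the odds ratio. Replacing the model with GEE is optional.

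The cost is wording and a few lines of code. Both factors are already collected, and no patient, procedure or sample size changes. It is best settled before the interim analysis, so that the choice cannot be seen as made after the data.

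### The interim efficacy analysis can stop the trial but has no numerical boundary, so the stated two-sided 5% level for the primary outcome is not secured

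*Protocol*

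**What the plan says.** Data monitoring (ii) of the Protocol plans an interim analysis of the primary endpoint. It takes place at the first of three triggers: after half of the "patients have been randomized, after 50% of the expected events have occurred, or after 12 months of" the start of the study. An independent statistician, blind to allocation, carries it out. Its purpose is to establish "whether the intervention has been proven for efficacy (beyond reasonable doubt"), after which the trial team decides whether to modify the study or end it early.

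Statistical methods gives one general rule: "For hypothesis testing, we will consider a probability level of less than 0.05 as statistically significant". It adds: "All statistical tests will be two-sided". Neither sentence makes an exception for the interim or adjusts the final test.

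Sample size states that 4,230 "reminders will be necessary to detect the difference between the two groups (power = 0.90", with alpha 0.05, "two-sided; 1:1 allocation". Data monitoring (i) separately allows the sample size and the 24-month recruitment period to be revised at the end of the roll-out.

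**The concern.** A look that can end the trial for efficacy is a second chance to declare success on the primary outcome. The error rate over both looks stays at 5% only if the interim threshold is fixed in advance and is either very strict or paid for at the final test. The Protocol does neither. Its interim criterion is verbal, and its one number is the ordinary 0.05, with the whole 0.05 also assigned to the final analysis.

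With no number in place, the meaning of proven efficacy could be settled after the interim data are seen. At stake are the type I error of the primary comparison and the credibility of any early stop. Neither can be repaired convincingly once the interim result is known.

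**Working it through.** **1. Is alpha already set aside in the sample size?** Inputs from Sample size: 5% versus 3%, power 0.90, two-sided alpha 0.05, 1:1 allocation.

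- Per arm without continuity correction: n = [1.960·√(2·0.04·0.96) + 1.2816·√(0.05·0.95 + 0.03·0.97)]² / 0.02² = 2,015.3, rounded up to 2,016 (4,032 in total).
- With continuity correction: n′ = (n/4)·[1 + √(1 + 4/(n·0.02))]² = 2,114.2, rounded up to 2,115, or **4,230 in total**. This is the Protocol's figure exactly.
- 4,230 × 1.10 = 4,653 (stated as 4,650), and 4,650 / 0.30 = 15,500 patients.

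The stated figure is a single-look design at the full 0.05. It contains no allowance for an interim look.

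**2. Type I error over two looks.** Under the null hypothesis the interim and final statistics (Z₁, Z₂) are bivariate normal with correlation √t, where t is the information fraction at the interim. The overall error is 1 − P(|Z₁|<c₁, |Z₂|<c₂). The Protocol does not give t. Its planning figures (50% of patients, or 12 of 24 months) imply about 0.5. Smaller values are assumptions, shown as a range.

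| t | p<0.05 at both looks (c₁ = c₂ = 1.960) | p<0.001, then p<0.05 (c₁ = 3.291, c₂ = 1.960) |
|---|---|---|
| 0.50 | 8.31% | 5.02% |
| 0.40 | 8.63% | 5.04% |
| 0.25 | 9.07% | 5.06% |
| 0.20 | 9.21% | 5.07% |

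**3. Cost of a proper boundary at t = 0.5.** The reference is the single-look design with power 0.900.

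- *Haybittle-Peto*, p<0.001 then p<0.05: power 0.900, with essentially no change in sample size.
- *Lan-DeMets O'Brien-Fleming-type*, spending 0.025 in each tail: nominal two-sided levels 0.0031 at the interim and 0.0490 at the end. Power is 0.899 over both looks, or 0.8985 if only the final test is counted.
- *The same spending function applied to a two-sided 0.05*: nominal levels 0.0056 and 0.0478, power 0.898, sample size × 1.008. This is a different convention, so its levels do not conflict with those above.

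These results hold for clustered reminders too, provided that the test statistic accounts for clustering and t is measured as statistical information.

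**The case against.** The strongest objection is that the Protocol never says the interim will be judged at 0.05. The 0.05 rule stands in Statistical methods. Data monitoring has its own criterion, and its wording reads more naturally as stricter than ordinary significance. On a p<0.001 reading there is almost no inflation. This stands: a reader might infer that the trial runs at 8–9%, and the document does not support that as a statement of fact.

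A second objection is that boundaries are often left to a statistical analysis plan, which may exist here but is not at hand. This stands in part. The missing detail alone would be no finding. But the Protocol itself fixes an efficacy look, its timing, its consequence, an unqualified 0.05 and a sample size that spends all of it. Taken together these do not deliver the level claimed.

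Third, low information fractions are hypothetical. The Protocol treats 12 months as the trial's midpoint, and none of its figures leads to 20% or 25%. This also stands, although it matters little: the error moves only from 8.3% to 9.2%.

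Finally, because the team decides on stopping, a reader might infer that blinding is lost at the interim. The document does not support this. The analyst is independent and blind to allocation, nothing says that comparative results go to the team, and an aggregate result would not reveal any patient's allocation.

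**Conclusion.** The point holds as a failure to secure the stated two-sided 5% level. The interim criterion has no number, the only number available is an unadjusted 0.05, and the final test already uses all of it. Depending on the threshold actually applied, the overall type I error lies between about 5.0% (p<0.001 at the interim) and 8.3% (0.05 at both looks, half information). It would be about 9% if 0.05 were used and the first trigger came at 25% of the information or less.

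The upper figures rest on two assumptions that the Protocol does not state: that 0.05 is the interim criterion, and that success may be claimed at either look. No conclusion about loss of blinding is drawn.

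**What to change.** Before the interim takes place, amend Data monitoring (ii) to state one numerical efficacy boundary, choosing one of these:

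- **Haybittle-Peto:** interim p<0.001, final p<0.05.
- **Lan-DeMets O'Brien-Fleming-type spending** at the information fraction actually observed, with the final test at the level that remains. At t = 0.5 this is about 0.003 and then 0.049. The fraction should use the planned total as revised by any recalculation under Data monitoring (i), and should allow for clustering by patient.

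Add to Statistical methods that the general p<0.05 rule does not apply to the interim look and, under spending, that the final level is the adjusted one. The three triggers, including the 12-month one, can stay, since alpha spending holds the error rate whichever comes first.

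The cost is a few sentences of amendment. Haybittle-Peto needs no change in sample size. Spending lowers power from 0.900 to between 0.898 and 0.899, depending on the convention, or raises the sample size by less than 1%.

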### 330 ***Harms***

331 We do not anticipate any harms (or other unintended effects) to study participants. Intervention and  
332 control groups will differ in the presence (intervention) or absence (control) of automatic reminders  
333 displayed on physicians' monitors. Patients assigned to the control group will receive usual care  
334 without the reminders. Nevertheless, we will consult an External Advisory Board in the event that the  
335 discontinuation of the study becomes an option due to unforeseeable reasons.

336

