### 188 *Selection and development of priority reminders*

189 In order to encourage the participation of the hospital staff within the study, we invited hospital  
190 representatives to assess the priority needs of the hospital wards and develop a set of reminders to  
191 address them. One topic of particular interest to the hospitals involved venous thromboembolism  
192 (VTE) prevention. The rationale for the prioritization of this condition is provided below:

193 (i) Despite evidence supporting the benefits of VTE prophylaxis based on the risk stratification process  
194 [35] as well as the availability of local hospital guidelines, the prophylactic drugs were inconsistently  
195 administered among patients.

196 (ii) The Hospital of Vimercate has an increasingly large population of elderly (aged > 65 years old) and  
 197 very elderly (aged > 80 years old) subjects, who have a higher risk of recurrent VTE and acute  
 198 pulmonary embolism [36].

199 (iii) Between 2010 and 2012, 45 patients (9.6%, 95% CI: 7.2–12.6) and 75 patients (16.0%, 95% CI:  
 200 12.9–19.5) died, respectively, within 30 days and 90 days after discharge due to VTE [36].

201 (iv) Research has shown the use of CDSSs to improve the assessment of patients' risk for VTE,  
 202 facilitate appropriate administration of prophylaxis interventions, and reduce the rate of symptomatic  
 203 VTE in hospitalized patients [37-53].

204

205 In order to develop the set of reminders for VTE prevention, the local hospital expert group proposed a  
 206 risk stratification process based on the Padua Score [54]. This formula calculates the overall risk (low  
 207 or high) of VTE for each patient using both clinical and surgical risk factors. Details of the underlying  
 208 algorithm are provided in Box 1.

209

210 Besides the VTE prevention therapy reminders, other scripts were chosen for development and tailored  
 211 to the hospital's needs. The following alerts were identified by the hospital's clinicians as of special  
 212 interest:

- 213 – Adjusting warfarin dose in atrial fibrillation,
- 214 – Alert on heparin-induced thrombocytopenia,
- 215 – Clopidogrel, prasugrel or ticagrelor and aspirin in acute ST-segment elevation myocardial infarction
- 216 (STEMI),
- 217 – Low-molecular-weight heparin as anticoagulant for patients with venous thromboembolism and
- 218 cancer,
- 219 – Selection of antithrombotic therapy in atrial fibrillation on the basis of the CHA2DS2VASc score,

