#### 254 *Study outcomes*

255 Primary outcome: the rate at which the medical problems, which are detected by the MediDSS software  
256 and reported through the reminders, are resolved (i.e. resolution rates).

257 Secondary outcomes: (i) resolution rates for the VTE prevention reminders, (ii) in-hospital all causes  
258 mortality (iii) VTE-related mortality, (iv) in-hospital morbidity for VTE-related causes, and (v) the  
259 length of hospital stay during the study period.

260

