659 **Box 1.** Description of algorithm for the use of venous thromboembolism prevention therapy

660

I. The algorithm incorporates the Padua Score [54], which uses ten common risk factors to identify patients at high risk for VTE. Each risk factor is individually weighted according to a point-based scale.

- Active cancer (defined as presence of methastases or recent chemotherapy), known trombophilic condition, and reduced patient mobility are each assigned a score of 3 points.
- Recent major surgery is assigned a score of 2 points.
- Advanced age (greater than 70 years), obesity (BMI greater than 30), bed rest, and hormone replacement therapy or oral contraceptives are each assigned a score of 1 point.

Patients are identified as high-risk for VTE if they accumulate a sum of 4 or more points. When the risk level is low, no medication is recommended; when the risk level is high, a prophylactic strategy using high dosage low-molecular-weight heparin is recommended.

II. The second part of the algorithm involved the Exclusion Criteria for the use of VTE Prophylaxis.

- Home Anticoagulant Therapy
- Contraindications to Pharmacologic Prophylaxis
- Active Bleeding

661

662

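### The Harms section anticipates no harm and no planned outcome identifies bleeding, although the priority VTE reminder recommends heparin prophylaxis and itself screens for bleeding

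*Protocol*

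**What the plan says.** **Harms.** The section opens with "We do not anticipate any harms (or other unintended effects) to study participants". The reason given is that the arms differ only in whether reminders appear on the physician's screen. No harm variable is named for collection or comparison. The one provision is "Nevertheless, we will consult an External Advisory Board in the event that the" trial's discontinuation comes into question for reasons that could not be foreseen.

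**Study outcomes.** The list reads "Secondary outcomes: (i) resolution rates for the VTE prevention reminders, (ii) in-hospital all causes" and continues "mortality (iii) VTE-related mortality, (iv) in-hospital morbidity for VTE-related causes, and (v) the" length of stay. Items (i), (iii) and (iv) are specific to VTE. Neither bleeding nor any other adverse effect of prophylaxis is listed.

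**Selection and development of priority reminders, and Box 1.** VTE prevention is the topic singled out as a priority. For patients scored as high risk, the Box 1 algorithm recommends prophylaxis with low-molecular-weight heparin. Its second part lists situations that exclude this: home anticoagulation, "Contraindications to Pharmacologic Prophylaxis" and active bleeding.

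**Data collection.** The trial takes admission "and discharge dates, diagnoses) data from the EHR archive on a daily basis", and logs every script activated in a patient's record. Under Intervention, reminders are generated for control patients too but not shown.

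**Data monitoring.** The interim analysis concerns the primary endpoint and asks about efficacy.

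**The concern.** The intervention is meant to change treatment: the primary outcome counts whether flagged problems get resolved. For the VTE prophylaxis reminder, resolution presumably means that prophylaxis is started, although the protocol does not define it reminder by reminder. A display that works is then no longer only a display. The protocol accepts this chain on the benefit side, where it measures VTE mortality and VTE morbidity, but drops it in the Harms section.

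The stated objective is the effect on clinical practice and quality of care. An outcome set that covers VTE in three ways and bleeding in none cannot support a balanced statement about the reminder that the hospital chose as its priority. The Advisory Board provision does not close the gap. It is tied to unforeseeable reasons, whereas Box 1 shows that bleeding was foreseen.

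**Working it through.** **1. Setting the sections side by side**

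| Section | What it implies about bleeding |
|---|---|
| Box 1, part I | The reminder can lead to more patients receiving heparin |
| Box 1, part II | Active bleeding and contraindications exclude the recommendation, so the risk is recognised |
| Harms | No harm or unintended effect is expected |
| Study outcomes | Three of five secondary outcomes are VTE-specific; none is bleeding |
| Data monitoring | The interim covers the primary endpoint only |

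The first two rows conflict with the third. The last two mean that no planned analysis would resolve the conflict.

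**2. The plan's own sample size**

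Inputs (Sample size section): 5% versus 3% resolved, power 0.90, two-sided 0.05, 1:1 allocation.

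- Pooled normal approximation: n′ = [1.960·√(2·0.04·0.96) + 1.282·√(0.05·0.95 + 0.03·0.97)]² / 0.02² = 2,015.3 per arm.
- Continuity correction: n = (n′/4)·[1 + √(1 + 4/(n′·0.02))]² = 2,114.2, rounded up to 2,115 per arm, or **4,230** in total. This matches the protocol.
- 4,230 × 1.10 = 4,653, stated as 4,650. Then 4,650 / 0.30 = 15,500 patients, or 7,750 per group.

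**3. How much extra treatment this implies**

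- Reminders per arm: 4,650 / 2 = 2,325.
- Extra resolved reminders in the intervention arm: 2,325 × (0.05 − 0.03) = 46.5, or **about 47**, spread over 262 international and 17 local reminders.
- With the 4.2-point improvement quoted from the cited systematic review instead: 2,325 × 0.042 = 97.65, or about 98.

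Extra patients given heparin because of the VTE reminder would be some unknown part of these counts.

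**4. How precise a bleeding comparison would be**

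The protocol gives no bleeding rate, so the control rates below are assumptions. The half-width of the 95% CI for the difference is 1.96·√(2p(1−p)/n). Multiplying by n turns it into bleeds per arm.

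| Assumed rate p | All patients, n = 7,750 | As bleeds per arm | As share of 46.5 | If 20% activate the script, n = 1,550 |
|---|---|---|---|---|
| 0.5% | ±0.22 points | 17.2 | 37% | ±0.50 points |
| 1% | ±0.31 points | 24.3 | 52% | ±0.70 points |
| 2% | ±0.44 points | 34.2 | 73% | ±0.99 points |

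The 20% share is also an assumption. At the planned 0.30 reminders per patient, it could not exceed 2,325 / 7,750 = 30%.

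The fourth column takes the extreme case in which all 46.5 extra resolutions are VTE reminders in different patients. Even then, between a third and three quarters of the newly treated would have to bleed for the excess to reach the half-width. The comparison is worth reporting but cannot rule out a harm of plausible size.

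**The case against.** **The data are not blind to bleeding.** All-cause mortality and length of stay would absorb fatal and severe bleeding, and diagnoses are held for everyone. This stands against a reading that a reader might take from the outcome list, that the trial has no way of seeing bleeding. The documents support less: nothing planned *identifies* it.

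**Adding bleeding would achieve little.** A reader might infer that 7,750 patients per arm give good power for safety. At 80% power, an assumed 1.0% control rate does allow 1.5% to be detected. But that difference is 0.005 × 7,750 ≈ 39 extra bleeds, or 83% of the 46.5 extra resolutions. The power argument fails on the protocol's own figures, and a null result could be over-read. It does not follow that bleeding should be omitted. The same dilution affects "in-hospital morbidity for VTE-related causes" and VTE-related mortality, which the protocol reports anyway.

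**Other anticoagulant content is protective.** "Alert on heparin-induced thrombocytopenia" and the warfarin–aspirin interaction text in Table 1 warn physicians about harm, so they do not contradict the Harms statement. The point rests on Box 1. It also follows that an all-patient comparison gives a net effect, mixing reminders meant to reduce bleeding with one that may increase it.

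**The Box 1 exclusions already protect patients.** They may lower the risk, but they do not measure it.

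**Physicians are the participants.** The ethics section says so, but the Harms section goes on to discuss patients and their care, and patients are the ones randomised.

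**A statistical analysis plan may cover it.** The Harms sentence and the outcome list are protocol content, and Protocol amendments requires a formal amendment to change outcomes.

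**Conclusion.** The point holds as an inconsistency and a one-sided outcome set. The Harms statement cannot stand beside Box 1, and the trial as planned could report on the benefit side of its priority reminder without a matching report on bleeding. No stated figure is wrong, and the primary analysis is unaffected.

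The likely numerical size is small under the planning assumptions: about 47 extra resolved reminders over all topics, or about 98 at the 4.2-point improvement. This rests on 0.30 reminders per patient, a figure taken from an earlier study of EBMeDS; a higher reminder rate among inpatients would raise it. The bleeding rates and the share of patients activating the script are assumptions, so the precision figures are only illustrative. The documents do not support the stronger inferences that bleeding is wholly invisible or that the trial is well powered to detect it.

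**What to change.** 1. In Harms, replace the statement that nothing is anticipated with one that names bleeding as a foreseeable harm of the prophylaxis reminder, so that the section agrees with Box 1.
2. In Study outcomes, add in-hospital bleeding, defined by a prespecified list of diagnosis codes, as a safety outcome. Analyse it at patient level by randomised group and report the difference with its 95% CI.
3. Report it twice: in all randomised patients, and in those whose record activates the VTE script. The second set can be formed in both arms because scripts run and are logged in both. Define it by first activation, since what is displayed afterwards could influence later data entry.

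**Cost.** A protocol amendment and a code list; no new data collection and no larger sample.

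**Limits to state with the result.** Coding is imperfect and may differ between arms because physicians are not blinded. Precision is limited, so a null finding is not evidence of safety. The all-patient figure is a net effect over reminders that act in different directions.

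This adds measurement only and takes no view on the prophylaxis rule or dose.
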